## Abstract

**Background:**

Moderate–severe traumatic brain injury (msTBI) stands as a prominent etiology of adult disability, with increased risk for cognitive impairment and dementia. Although some recovery often occurs within the first year post-injury, predicting long-term cognitive outcomes remains challenging, partly due to the significant pathophysiological heterogeneity of TBI, including acute cerebrovascular injury. The primary aim of our recently funded study, cerebral autoregulation, brain perfusion, and neurocognitive outcomes after traumatic brain injury (CAPCOG-TBI), is to determine if acute cerebrovascular dysfunction after msTBI measured using multimodal non-invasive neuromonitoring is associated with cognitive outcome at 1-year post-injury.

**Methods:**

This longitudinal observational study will be conducted at two Level 1 trauma centers in Texas, USA, and will include adult patients with msTBI, and/or mild TBI with neuroimaging abnormalities. Multimodal cerebral vascular assessment using transcranial Doppler and cerebral near-infrared spectroscopy (NIRS) will be conducted within 7-days of onset of TBI. Longitudinal outcomes, including cognitive/functional assessments (Glasgow Outcome Scale and Patient-Reported Outcomes Measurement Information System), cerebral vascular assessment, and imaging will be performed at follow-ups 3-, 6-, and 12-months post-injury. We aim to recruit 100 subjects with msTBI along with 30 orthopedic trauma controls (OTC). This study is funded by National Institute of Neurological Disease and Stroke (NINDS) and is registered on Clinicaltrial.org (NCT06480838).

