## Background and rationale

Nonfatal traumatic brain injury (TBI) stands as a prominent etiology of adult disability, presenting substantial morbidity for the victims, their families, and society at large, with several negative impacts, including cognitive impairment (1, 2). Moderate–severe TBI (msTBI), defined as a Glasgow Coma Scale (GCS) score of 3–12 on admission carries the largest burden of morbidity and mortality (2), with notable variability in clinical outcomes following msTBI. Cognitive impairment, including impaired memory, slow processing speed, and diminished attention span, is particularly prevalent after msTBI (3–5). Although some recovery typically occurs within the first year post-injury (3), accurately predicting long-term cognitive outcomes remains challenging.

This challenge is partly due to the high pathophysiological heterogeneity of TBI, particularly the occurrence of acute cerebrovascular injury that is common following msTBI (6). Acute cerebrovascular injury after msTBI includes vasospasm of larger cerebral arteries, trauma-induced vascular damage at smaller vessel levels, and disruption of the blood–brain barrier and endothelium due to shear (6, 7). In addition, the injury processes involve altered brain metabolism, impaired waste clearance, and neuroinflammation, leading to brain hypoperfusion, disrupted neurovascular coupling, impaired cerebral autoregulation (CA), as well as inefficient adjustments in cerebral blood flow to changes in perfusion pressure (8–10). There is some evidence suggesting that acute cerebrovascular dysfunction following TBI, as assessed by cerebral blood flow and CA by transcranial doppler (TCD), is associated with unfavorable functional outcomes in those with Glasgow Outcome Scale scores less than 3 (10). Nevertheless, a significant gap persists in the literature regarding longer-term follow-ups and comprehensive assessments of cerebrovascular function alongside cognitive function for this patient population.

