### Study design

This study will be a prospective, longitudinal observational study. We propose to recruit 100 subjects with TBI and 30 orthopedic trauma controls within the first week after the initial injury, matching them for age range and gender. We will follow these patients with physiological, imaging, and cognitive/functional outcome measures over a year (Figure 1).

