#### Study population

Patients aged between 18 and 80 years old, within 1-week post-injury, and admitted to the hospital for moderate to severe TBI and/or mild TBI with neuroimaging abnormalities are eligible for inclusion (see Table 1). Additionally, individuals with orthopedic injury without TBI can participate as a control group if they meet the inclusion criteria outlined in Table 1 and do not meet any of the exclusion criteria.

**Table 1 tab1:** Eligibility criteria.

Inclusion Criteria for TBI Group A documented moderate to severe TBI posttraumatic Amnesia (PTA) > 24 h Loss of consciousness (LOC) >30 min Global cognitive score (GCS) <13, or Intracranial neuroimaging abnormalities (Head CT or MRI) Mild TBI with abnormalities on imaging exam. Ages 18–80 years-old 1 week post injury and admitted to the hospital for TBI. All participants must be fluent in English or Spanish. Inclusion Criteria for non-TBI Orthopedic Control Group: Abbreviated Injury Score of ≤4 (not life threatening) for extremity and/or pelvis injury and/or rib fracture Without evidence of TBI based on history or head CT 1 week post injury and admitted to the hospital for trauma. All participants must be fluent in English or Spanish. Exclusion Criteria for the study Significant polytrauma that would interfere with follow-up and outcome assessment. Major debilitating baseline mental health disorders, major debilitating neurological disease, impairing baseline awareness, cognition, or validity of follow-up and outcome assessment. Significant history of pre-existing conditions that would interfere with follow-up and outcome assessment (e.g., end-stage cancers). Patients on psychiatric hold. Prisoners or patients in custody, pregnancy, low likelihood of follow-up (e.g., participants or family indicating low interest, residence in another state or country, homelessness or lack of reliable contacts). Current participant in an interventional trial (e.g., drug, device, behavioral). Penetrating TBI, spinal cord injury with ASIA score of C or worse and contraindications to MRI.

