## Discussion

CAPCOG_TBI study is an observational study that will investigate long- term cognitive outcomes after msTBI at three level 1 trauma centers in Texas, USA. The main purpose of the study is to determine if acute cerebrovascular dysfunction after msTBI is associated with cognitive outcome at 1-year post-injury. To our knowledge, no prospective studies have evaluated cerebral vascular assessment in the acute phase and compared it with long-term cognitive outcomes in msTBI patients.

The rationale for the CAPCOG study arises from the significant variability in clinical outcomes and brain lesions resulting from trauma, which can range from no measurable impairment to a vegetative state (12, 61). This variability presents a considerable challenge in predicting and prognosticating cognitive outcomes following msTBI.

Previous studies have explored relationships between cerebrovascular dysfunction and cognitive outcomes at 6 and 12 months post-TBI (10, 62). However, these analyses were performed retrospectively. Unfortunately, the largest prospective studies published on this topic, analyzing long-term function outcomes, did not include cerebrovascular assessments (3, 11). Nonetheless, the acute cerebrovascular dysfunction assessed by CA in TBI may play a role in cognitive outcomes and prediction models. Therefore, this large longitudinal prospective study meets the urgent need to understand temporal associations of CA recovery with functional and cognitive recovery during the critical time window of 12 months after TBI.

Another point to raise is that the majority of studies assessing functional outcomes have relied exclusively on the GOSE, which is a crude measure of outcome. Robust use and the combination of more detailed cognitive assessments and functional scales are crucial for a comprehensive analysis of cognitive function outcomes, such as NIHTB-CB, RAVLT, WAIS-IV PSI, FIM, and PROMIS PROPr scales. To mitigate potential limitations in cognitive assessment, all of these scales will be employed in the CAPCOG_TBI study.

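### The target, main aim and conclusion are stated for msTBI (GCS 3–12), but the design recruits and pools a TBI cohort that includes mild cases with positive imaging

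*Protocol article*

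**What the plan says.** Background and rationale introduces the population as "Moderate–severe TBI (msTBI), defined as a Glasgow Coma Scale (GCS) score of 3–12 on admission".

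The abstract's Methods say the study "will include adult patients with msTBI, and/or mild TBI with neuroimaging abnormalities", and a few sentences later give the target: "We aim to recruit 100 subjects with msTBI along with 30 orthopedic trauma controls (OTC"). The Study population text repeats the wider eligibility: patients "admitted to the hospital for moderate to severe TBI and/or mild TBI with neuroimaging abnormalities are eligible for inclusion". Table 1 lists four features under moderate to severe TBI: amnesia beyond 24 hours, loss of consciousness beyond 30 minutes, GCS below 13, or an intracranial imaging abnormality. It then adds a separate entry, "Mild TBI with abnormalities on imaging exam". No cap, quota or stratification by severity is stated.

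Study design describes the same 100 differently: "We propose to recruit 100 subjects with TBI and 30 orthopedic trauma controls within the first week after the initial injury". Power and sample size also gives TBI = 100 and control = 30, and Aim of the study states all three aims for TBI.

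The abstract's Background states the primary aim for msTBI. The Discussion gives the main purpose as to "determine if acute cerebrovascular dysfunction after msTBI is associated with cognitive outcome at 1-year post-injury", and the closing Conclusion also refers to msTBI. The primary model (Statistical methods: outcomes) is a multiple linear regression of the 1-year fluid composite on the autoregulation indices. Initial GCS is one of the adjusting variables.

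**The concern.** Under the article's own definition, a patient with GCS 13–15 and a positive scan is not an msTBI patient, yet can be enrolled and counted among the 100. The abstract's target therefore describes a group that the design does not guarantee.

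The consequence is for inference as well as wording. Adjusting for initial GCS lets the expected cognitive score vary with severity. It does not let the relation between autoregulation and cognition vary with severity: one slope is fitted across everyone. If that slope is then reported as the answer for msTBI, the claim is narrower than the data behind it. The article's own rationale is the heterogeneity of TBI, so it is weakly placed to take a common slope for granted.

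**Working it through.** **1. Who the 100 are.**

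| Place in the protocol article | Population named |
|---|---|
| Background and rationale | msTBI = admission GCS 3–12 |
| Abstract, Methods (inclusion) | msTBI and/or mild TBI with imaging abnormality |
| Abstract, Methods (target) | 100 msTBI |
| Aim of the study; Study design; Power and sample size | TBI |
| Study population and Table 1 | Moderate to severe, and/or mild with imaging abnormality |
| Abstract, Background (primary aim); Discussion; Conclusion | msTBI |

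The total is the same 100 in the abstract, Study design, and Power and sample size. It is therefore the whole TBI cohort, not an msTBI quota with mild cases added on top.

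**2. Table 1 against the definition.** As printed, an imaging abnormality satisfies the moderate to severe list, and the same feature also defines the mild entry. A GCS 15 patient with a positive scan fits both lines, and does not fit the GCS 3–12 definition.

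**3. The plan's own power figure.** Inputs from Power and sample size: 117 evaluable participants (90 TBI + 27 controls), R² = 0.35 for 6 control variables, an R² increase of 0.053 from 2 tested variables, two-sided 5%.

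- Effect size: f² = 0.053 / (1 − 0.35 − 0.053) = 0.053 / 0.597 = 0.0888
- Degrees of freedom: 2 and n − 2 − 6 − 1 = n − 9
- Noncentrality: λ = n × f²
- Power: probability that a noncentral F(2, n − 9, λ) exceeds the 5% critical value of the central F

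At n = 117, λ = 10.39 and power = 81.95%, which matches the stated 82%. The attrition step also reproduces: 117/0.9 = 130, 90/0.9 = 100, 27/0.9 = 30. The calculation is sound for 90 TBI completers of any eligible severity.

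**4. Illustration for a GCS 3–12 analysis.** The documents do not give the mild share, so the splits below are assumed. The 27 controls are kept, as in the plan, and the R² values are assumed unchanged in the stratum.

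| TBI completers with GCS 3–12 (of 90) | n with 27 controls | λ | Power |
|---|---|---|---|
| 90 (no mild cases) | 117 | 10.39 | 82.0% |
| 72 (80%) | 99 | 8.79 | 74.5% |
| 45 (50%) | 72 | 6.39 | 59.1% |

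**The case against.** The best defence is that the operative sections are consistent. The formal aims, the design and the sample size all say TBI, the mild inclusion is disclosed in the abstract itself, and pooling across severity with adjustment for GCS, amnesia and head CT is a legitimate choice for an observational study. Table 1 can also be read as a broader eligibility definition of moderate to severe TBI, and its nesting may have been lost when the text was extracted. Most of this stands. It makes the fault one of inconsistent labelling, not concealment or a wrong sample size. It does not remove the conflict, because the running text, without Table 1, both admits mild TBI and calls the 100 msTBI.

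It is also fair to say that a severity interaction or a stratum model is something an article commonly leaves to the analysis plan. Its absence here is not the finding. The finding is that msTBI conclusions are announced for a pooled model.

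A reader might infer three stronger things that the documents do not support:

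- **That the study is underpowered because of this.** The planned analysis does not exclude mild cases, and its 82% holds. Dropping the controls as well would give 70.0% at n = 90 and 38.5% at n = 45. The fall from 82% to 70% has nothing to do with mild cases; it comes only from removing 27 controls that the plan counts.
- **That the analysed sample will be mostly mild.** In-person testing, MRI contraindications and the exclusion for low likelihood of follow-up could tilt it that way. Consent by a representative and follow-up of patients still in hospital pull in the other direction. No figure is given for either.
- **That the slope differs by severity.** This is possible, but nothing in the article shows it.

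**Conclusion.** The point holds as a mismatch between the population named and the population recruited and modelled. The abstract's 100 msTBI subjects are 100 TBI patients of mixed severity, and the pooled primary slope does not by itself answer the msTBI question posed in the abstract, Discussion and Conclusion. The stated sample size and power are unaffected if the target is read as TBI.

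The size of the mismatch cannot be computed, since the mild share is unknown. Power for an msTBI-specific answer would be about 75% with 72 and about 59% with 45 of the 90 TBI completers at GCS 3–12. Both figures assume that the controls stay in and that R² = 0.35 and the 0.053 increase carry over to the stratum.

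**What to change.** 1. Use one definition of msTBI throughout, and reconcile the two Table 1 entries so that a patient with GCS 13–15 and positive imaging falls in only one category.
2. Restate the recruitment target, primary aim, main purpose and conclusion as TBI (moderate–severe, or mild with imaging abnormalities), in line with the aims, design and sample-size sections.
3. Repeat the primary model in the admission GCS 3–12 stratum, with an autoregulation × severity term (GCS 3–12 against 13–15) as supportive evidence, and draw msTBI-specific conclusions only from that stratum. If the unseen analysis plan already has these models, the article need only tie its msTBI claims to them.
4. Report the number of TBI patients in each severity group.

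The cost is a wording change, one stratum model and one interaction term, all on data already planned. Enrolment and sample size do not change. The price is a wider interval for the msTBI estimate than for the pooled one.

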**Expected results:**

We anticipate that msTBI patients will exhibit impaired cerebrovascular function in the acute phase compared to the OTC group. The severity of cerebrovascular dysfunction during this stage is expected to inversely correlate with cognitive and functional outcomes at 1-year post-injury. Additionally, recovery from cerebrovascular dysfunction is expected to be linked to cognitive recovery.

**Conclusion:**

The results of this study could help to understand the contribution of cerebrovascular dysfunction to cognitive outcomes after TBI and pave the way for innovative vascular-focused interventions aimed at enhancing cognitive recovery and mitigating neurodegeneration following msTB. In addition, its focus toward personalized medicine to aid in the management and prognosis of TBI patients.

## Background and rationale

Nonfatal traumatic brain injury (TBI) stands as a prominent etiology of adult disability, presenting substantial morbidity for the victims, their families, and society at large, with several negative impacts, including cognitive impairment (1, 2). Moderate–severe TBI (msTBI), defined as a Glasgow Coma Scale (GCS) score of 3–12 on admission carries the largest burden of morbidity and mortality (2), with notable variability in clinical outcomes following msTBI. Cognitive impairment, including impaired memory, slow processing speed, and diminished attention span, is particularly prevalent after msTBI (3–5). Although some recovery typically occurs within the first year post-injury (3), accurately predicting long-term cognitive outcomes remains challenging.

This challenge is partly due to the high pathophysiological heterogeneity of TBI, particularly the occurrence of acute cerebrovascular injury that is common following msTBI (6). Acute cerebrovascular injury after msTBI includes vasospasm of larger cerebral arteries, trauma-induced vascular damage at smaller vessel levels, and disruption of the blood–brain barrier and endothelium due to shear (6, 7). In addition, the injury processes involve altered brain metabolism, impaired waste clearance, and neuroinflammation, leading to brain hypoperfusion, disrupted neurovascular coupling, impaired cerebral autoregulation (CA), as well as inefficient adjustments in cerebral blood flow to changes in perfusion pressure (8–10). There is some evidence suggesting that acute cerebrovascular dysfunction following TBI, as assessed by cerebral blood flow and CA by transcranial doppler (TCD), is associated with unfavorable functional outcomes in those with Glasgow Outcome Scale scores less than 3 (10). Nevertheless, a significant gap persists in the literature regarding longer-term follow-ups and comprehensive assessments of cerebrovascular function alongside cognitive function for this patient population.

The most significant recovery of cognitive function usually occurs during the first 6 months post-injury, but the patients may continue to experience improvement afterward (3, 11). The risk factors for poor cognitive recovery include older age, more severe initial injury, lower pre-injury work productivity, and lower discharge functional status (12). However, currently, none of these clinical factors can reliably predict cognitive outcomes following msTBI (12). Conversely, studies have suggested cerebrovascular dysfunction defined as persistent CA and regional brain perfusion alterations utilizing TCD is associated with lower cognitive performance in the chronic phase of TBI (13–17).

The literature for msTBI outcomes is limited by insufficient long-term follow-up durations and suboptimal evaluations of cognitive function. Additionally, the role of acute cerebrovascular injury and its recovery in relation to cognitive recovery has not been studied prospectively. The Cerebral autoregulation, brain perfusion, and neurocognitive outcomes after traumatic brain injury (CAPCOG-TBI) study is a prospective observational study funded by National Institute of Neurological Disease and Stroke (NINDS) and aims to investigate the association between acute cerebrovascular dysfunction after msTBI and cognitive outcomes at 1-year post-injury. Moreover, it seeks to assess longitudinal changes in cerebrovascular function focusing on dynamic cerebral autoregulation and brain perfusion, as well as its impact on cognitive recovery during the first year post-injury.

## Methods and analysis

### Aim of the study

Our primary research aim is to determine if acute cerebrovascular dysfunction after TBI is associated with cognitive outcome at 1-year post-injury. Secondly, to determine the temporal associations between the recovery of cerebrovascular function and cognitive outcomes after TBI. The third aim is to determine the temporal associations of acute cerebrovascular dysfunction and its recovery with imaging biomarkers of neurodegeneration after TBI.

We expect that the severity of cerebrovascular dysfunction during the acute stage will be inversely associated with cognitive outcomes and functional outcomes at 1-year post-injury. Additionally, we also anticipate that, compared to an orthopedic control (OTC) group with no TBI history, the TBI patients will exhibit impaired dynamic CA in the acute phase. Assessments of CA during the acute stage of TBI are expected to independently predict functional and cognitive outcomes at 1-year post-injury. The results of this study could pave the way for innovative vascular-focused interventions aimed at enhancing cognitive recovery and mitigating neurodegeneration following TBI (Figure 1).

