### Data collection

#### Clinical data

In order to standardize data collection and enable comparison, the collection of clinical variables will adhere to a predefined set of National Institutes of Health/National Institute of Neurological Disorders and Stroke Common Data Elements (NIH/NINDS CDEs). These variables encompass a wide range of information including demographics, social status, general health history, injury-related events, physical and neurological examination findings, laboratory test results, vital signs, clinical imaging findings on the initial head computed tomography (CT), hospitalization details, discharge information, and inpatient rehabilitation data. These variables will be collected through chart review and/or patient or family interviews (18, 19).

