### Power and sample size

This study is powered to examine the relationship between the primary outcome of NIHTB_CB fluid composite score at 1-year postinjury and dynamic CA indices derived from frequency-domain analysis during the acute stage of TBI (i.e., <1-week postinjury). According to our previous study (13), the dynamic CA transfer function phase at low frequency range was positively correlated with NIHTB_CB fluid composite score (i.e., a higher phase, a better CA, was associated with better cognitive score), with the coefficient of determination (
$R^{2}$
) of 0.35 (or Pearson correlation coefficient = −0.593). Based on this information, it is estimated that 117 participants (i.e., a cohort of TBI *n* = 90 and orthopedic controls *n* = 27) will provide 82% power at a 5% two-sided significance level to detect a 0.053 increase in 
$R^{2}$
 attributed 2 additional dynamic CA variables (transfer function gain and coherence), adjusting for 6 confounding factors (initial GCS, posttraumatic amnesia, head CT scan, age, sex, and education) in a multiple regression model, where 
$R^{2}=$
0.35 when only the control factors are included in the model (NCSS PASS 16). With a 10% attrition rate, the total sample size of *n* = 130 participants (TBI = 100, control = 30) are required to be enrolled for this study.

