#### Statistical methods: outcomes

For the primary analysis, multiple linear regression models will be performed to examine the associations of dynamic CA indices on the primary outcome of NIHTB_CB fluid composite score at 1 year post injury, adjusted by potential confounders (i.e., initial GCS, posttraumatic amnesia, head CT scan, age, sex, etc.). The parsimonious model will be selected via the automatic model selection algorithms, including forward, backward, and stepwise selection. Multicollinearity will be evaluated using variance inflation factors, and the issue of overfitting will be assessed through 10-fold cross-validation. For the secondary analyses, secondary outcomes, including CA/CBF and other continuous cognitive measures, R-GOSE score as well as health-related PROMIS measures at 1-year postinjury, will be analyzed separately through the same analytical approach. Sensitivity analyses of the outcomes will be performed to assess the robustness of the findings, including model diagnostics, outlier assessments, distributional assumptions, and missing data. Data transformation will be made if the normality assumption is violated.

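### The primary model names no vascular-comorbidity or pre-injury-function term, and automatic selection can drop the confounders it does name, so independent prediction by acute CA is not secured

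*Protocol article*

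**What the plan says.** Under Aim of the study, the protocol article states the expectation: "Assessments of CA during the acute stage of TBI are expected to independently predict functional and cognitive outcomes at 1-year post-injury". The primary outcome is the NIH Toolbox fluid composite at one year.

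The adjustment set for that regression is described twice:

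- Power and sample size gives a closed list of six: "adjusting for 6 confounding factors (initial GCS, posttraumatic amnesia, head CT scan, age, sex, and education) in a multiple regression model".
- Statistical methods: outcomes gives a list that omits education and is left open at the end: "adjusted by potential confounders (i.e., initial GCS, posttraumatic amnesia, head CT scan, age, sex, etc".

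The second section then adds: "The parsimonious model will be selected via the automatic model selection algorithms, including forward, backward, and stepwise selection". It does not say that any confounder is kept in regardless of the algorithm.

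Three other places bear on pre-injury status:

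- Background and rationale gives the risk factors for poor cognitive recovery as "older age, more severe initial injury, lower pre-injury work productivity, and lower discharge functional status".
- Clinical data says that the collected variables cover, among others, "demographics, social status, general health history, injury-related events".
- The eligibility table excludes major debilitating mental or neurological disease "impairing baseline awareness, cognition, or validity of follow-up and outcome assessment", and pre-existing conditions serious enough to interfere with follow-up. Common vascular disease is not excluded.

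Cognition is first tested at the 3-month visit.

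**The concern.** Long-standing vascular disease could plausibly lower both autoregulation and fluid cognition before any injury, and low prior function could be linked to both in the same way. Adults aged 18 to 80 with such histories can enrol. If neither factor is in the model, part of what they contribute is credited to acute CA.

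The article itself treats work productivity before the injury as prognostic, yet leaves it out of both lists. Education, the one named factor that stands in for prior ability, appears in one list and not in the other. Selection by algorithm adds a second weakness: a confounder matters because of its joint relation to exposure and outcome, and a stepwise rule can discard it for a weak association with the outcome alone in about 117 people.

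At stake is how a positive primary result may be worded. A claim of independence needs the main common causes to be in the model and to stay there.

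**Working it through.** **Inputs from Power and sample size:** N = 117 analysed (90 TBI + 27 controls), 6 covariates with R² = 0.35, 2 CA variables adding 0.053 to R², two-sided 5% level, stated power 82%.

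**1. Reproduce the plan's figure.**
- f² = 0.053 / (1 − 0.35 − 0.053) = 0.053 / 0.597 = 0.0888.
- Noncentrality λ = 117 × 0.0888 = 10.39.
- Degrees of freedom: 2 and 117 − 2 − 6 − 1 = 108.
- Noncentral F power = 0.8195, which agrees with 82%. Attrition: 117 / 0.9 = 130. The stated figures are sound.

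**2. Put the design effect on a correlation scale.** Partial R² = 0.053 / 0.65 = 0.0815. The partial correlation is √0.0815 = 0.286, a multiple partial correlation for the pair of CA variables.

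**3. Effect of one omitted pre-injury factor when CA has no effect of its own.** Let a be the factor's partial correlation with the CA pair and b its partial correlation with the fluid score, both after the six covariates. Then the spurious partial r = ab, the spurious R² increment = 0.65 × (ab)², f² = (ab)² / (1 − (ab)²), and λ = 117 × f², tested on 2 and 108 df. The values of a and b are assumptions; the documents give none.

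| a = b | Spurious partial r | Spurious R² increment | Share of 0.053 | Rejection rate (nominal 5%) |
|---|---|---|---|---|
| 0.2 | 0.04 | 0.001 | 2% | 6% |
| 0.3 | 0.09 | 0.005 | 10% | 13% |
| 0.4 | 0.16 | 0.017 | 31% | 32% |
| 0.5 | 0.25 | 0.041 | 77% | 69% |

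To reproduce the whole design effect, a = b = 0.0815^(1/4) = 0.53 is needed. These rates assume that all six covariates stay in the model; the effect of stepwise selection is not modelled.

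**4. Cost of extra covariates.** With 7 to 10 covariates in all, and R² = 0.35 and the increment of 0.053 unchanged, power is 0.8194 to 0.8191. If three added covariates also absorb part of the CA increment (assumed, control R² held at 0.35), power is 0.685 at an increment of 0.04, 0.545 at 0.03 and 0.379 at 0.02. If they raise the control R² to 0.40 as well, the figure at 0.04 is 0.724.

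**The case against.** The strongest reply is that this is a condensed article with an open covariate list, and a full list commonly belongs to the SAP. Health history and social status are collected, so nothing prevents their use. That reply has force against calling the omission an error of design. It does not dispose of the point: the article states the set twice, the two statements differ on education, a factor that it calls prognostic is in neither, and the selection rule it fixes protects none of them.

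Three stronger readings are tempting, and the documents do not support them:

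- *No pre-injury factor beyond age and sex is adjusted for.* The power section names education for this regression.
- *A positive result would be equally well explained by pre-injury status.* At assumed correlations of 0.2 to 0.3, the spurious partial correlation is 0.04 to 0.09 against a target of 0.286. Only about 0.53 with both CA and outcome would match it.
- *The lack of a pre-injury cognitive test is a flaw.* It is inherent in a cohort recruited after unplanned trauma, and gross baseline impairment is excluded.

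It is also fair to say that the primary aim is worded as an association, and that independent prediction is an expectation and not a concluded result. The article does not say whether the fluid composite is raw or demographically normed.

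**Conclusion.** The point holds as a limited one. The stated confounders contain no vascular-comorbidity or pre-injury-function term, the two lists disagree on education, and automatic selection guarantees none of them a place. Pre-injury disease or low prior function could therefore partly explain an association between acute CA and the 12-month score.

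Moderate confounding (0.3 to 0.4 with each) would raise the false-positive rate from 5% to roughly 13% to 32%, while accounting for only about 10% to 31% of the assumed R² increment. Those figures rest on assumed correlations, a single omitted factor and no true CA effect. The sample size calculation is not in question. What is not yet supported is the word independently.

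**What to change.** - Make Power and sample size and Statistical methods: outcomes agree on the confounder list, including education.
- Force into the primary model, outside automatic selection, education, a vascular-risk count from the general health history and pre-injury work status from the social history. Confirm first that the common data elements record these items; the article names only the broad categories.
- Use the NIH Toolbox language score in a sensitivity analysis only. It is first measured at 3 months, and the injury may lower it.
- State in advance that if the CA terms do not survive this adjustment, the result is reported as an association and not as independent prediction.

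The cost is plan wording and a few degrees of freedom, with no new data if the items are recorded. Power stays at about 0.82 if the CA increment is unchanged. It falls if the added terms absorb part of the 0.053, and in that case that part was not independent of pre-injury status.
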